### Outcomes

#### Primary outcome

The primary outcome is heart failure (either clinical or subclinical). In this study, New York Heart Association (NYHA) Functional Classification will be used to evaluate the extent of clinical heart failure. Left ventricular ejection fraction (LVEF) less than 50% or a drop of more than 15% from baseline is defined as subclinical heart failure in this study. Ejection fraction is measured using multigated acquisition (MUGA) scan in all participants. MUGA scans will be performed by the same physician; this physician is not involved in recruitment of the study.

#### Secondary outcomes

Secondary outcomes include all-cause mortality, cardiac death, electrocardiogram (ECG) findings, left ventricular diastolic function, longitudinal systolic strain and velocities measured by tissue Doppler imaging, cardiac biomarkers, such as troponin I (TnI), brain natriuretic peptide (BNP), and creatine kinase isoenzymes (CK-MB) [23].

#### Safety outcomes

Safety outcomes include both clinical and subclinical measures. Routine physical examination will be performed on all participants during the study period; any unexpected symptoms or signs will be recorded as clinical measures. Routine complete blood count, blood chemical analysis, urinalysis, fecal examination, liver function tests, and renal function tests will be performed as subclinical measures to assess safety for all participants.

### Data collection and management

CRFs will be used to collect data. To promote data quality and accuracy, one trained investigator will complete the CRFs and a second investigator will independently review all CRFs. Once data collection is complete, all data will be entered in duplicate into a computer database using EpiData 3.1 software (The EpiData Association, Denmark, Europe), by two individual data managers working independently through separate authorized identification codes and passwords. Figure 2 summarizes the study schedule of enrollment, interventions, and assessments according to the SPIRIT 2013 statement. Regular backups and off-site storage will be performed. The original CRFs and any other paper records will be kept on file at the clinical study center for 5 years after completion of the study.

**Fig. 2 Fig2:**
[figure not shown]
Schedule of enrollment, interventions and assessments (using the SPIRIT 2013 statement [26]). ECG electrocardiogram, LVEF left ventricular ejection fraction, MUGA multigated acquisition, LV left ventricle, CK-MB creatine kinase isoenzymes, TNI troponin I, BNP brain natriuretic peptide, NYHA New York Heart Association

### Data and safety monitoring

Both adverse events (AEs) and serious adverse events (SAEs) will be assessed in this study. AEs are defined as unintended or unfavorable clinical symptoms, signs, laboratory results, or diseases that do not necessarily have a causal relationship with the study intervention. AEs in all participants in this clinical trial will be recorded at every visit. Details of all AEs will be recorded, including starting and ending date, grade (using the National Cancer Institute “Common terminology criteria for adverse events (NCI-CTCAE v 4.03)” [24]), and relation to the study medication. SAEs are defined as death, illness requiring hospitalization, events deemed life-threatening, events that result in persistent or significant disability or incapacity, a congenital anomaly or birth defect, or other important medical conditions. The Data and Safety Monitoring Board (DSMB) for this study will comprise one independent statistician, one senior pharmacist, one physician, and one individual with experience supervising a clinical trial. All members of the DSMB are independent from the trial sponsor and have no competing interests. The DSMB will organize a conference before allocation of the study and will review the trial documentation at least once to ensure that the trial is being conducted according to the trial protocol and GCP principles and that the data and SAEs are accurately and appropriately recorded on the CRF. All SAEs will be reported to the DSMB, ethics committees, sponsors, and the CFDA immediately. If a patient experiences a SAE, the DSMB has permission to unblind the case in the event of a medical emergency.

### Sample size calculation

The study aims to detect the cardioprotective effects of *P. grandiflorum* in patients with early breast cancer receiving anthracycline-based chemotherapy. Sample size was calculated on the basis of the primary outcome. Since no randomized controlled trials (RCTs) have been previously performed on the cardioprotective effects of *P. grandiflorum* in patients receiving anthracycline-based chemotherapy, we proposed this study to evaluate the feasibility of a large-scale clinical trial. Anticipating a 20% dropout rate, a total of 120 patients, with 60 patients in each group, will be recruited for the pilot study.

### Statistical analysis

An independent, professional statistician will perform the data analysis for the results and the AEs. Intention-to-treat (ITT) analysis will be carried out in all participants who complete the clinical trial. Missing data will be adjusted for using the last observation carried forward (LOCF) principle to obtain a complete database. Continuous data will be presented as means and standard deviations $$ \left(\overline{X}\pm SD\right) $$, or medians and quartiles. The comparability of the two groups will be assessed using the independent samples *t* test for continuous variables and the chi-square (χ^2^) test or Wilcoxon test, when appropriate, for categorical variables. The cumulative dose of anthracycline to cause cardiotoxicity will be estimated in each group using Kaplan-Meier curves; differences between the curves will be assessed using the log-rank method. The crude and adjusted hazard ratios and 95% confidence intervals will be estimated using a Cox proportional hazards regression model. All analyses will be performed using IBM SPSS software version 19 (IBM, Armonk, NY, USA). A two-tailed *P* value <0.05 was set for statistical significance.

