### Hypothesis

We hypothesize that: (1) after 12 weeks, fewer patients taking *P. grandiflorum* will develop cardiac damage compared with patients receiving placebo, (2) *P. grandiflorum* will be safe at the dosage used in this trial, and (3) *P. grandiflorum* will have similar effects to placebo on non-cardiac anthracycline toxicities.

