### Intervention

Enrolled patients will be randomly allocated to either the treatment or control group. Patients in the treatment group will receive anthracycline-based chemotherapy with *P. grandiflorum* granules. Patients in the control group will receive anthracycline-based chemotherapy with placebo granules. All patients, regardless of which group they are randomized to, will be instructed to dissolve one package of granules in 150 mL hot water twice daily for 12 consecutive weeks. Participants will be withdrawn if they take any other CHM or Western medication to treat heart disease during the 12-week intervention period or if they are not willing to take the study drug. Treatment for other conditions, such as hypertension, diabetes mellitus, and other chronic diseases, will be permitted during the intervention. The name, duration, and dosage of any other drugs taken during the 12-week intervention period will be recorded in each patient’s case report form (CRF). In order to assess adherence to taking the intervention medication, each participant will be asked to undergo laboratory tests at each follow-up appointment. Patients will also be asked to return any unused drug granules. Participants who return more than 10% of the total allotted granules will be defined as nonadherent. Patient-reported reasons for nonadherence will be recorded on the CRF.

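### The only analysis population the protocol names is trial completers, and the adverse-event comparison is given no other, although safety data are collected on everyone

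*Protocol article*

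**What the plan says.** The Statistical analysis section of the protocol article begins: "An independent, professional statistician will perform the data analysis for the results and the AEs". The next sentence is: "Intention-to-treat (ITT) analysis will be carried out in all participants who complete the clinical trial". The missing-data rule follows: "Missing data will be adjusted for using the last observation carried forward (LOCF) principle to obtain a complete database". The article names no other analysis population.

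The Intervention section withdraws patients who take other Chinese herbal or Western medication for heart disease during the 12 weeks, "or if they are not willing to take the study drug". The sample size section anticipates 20% dropout from 120 patients, 60 per arm.

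The safety sections are written for everyone:
- Data and safety monitoring: "AEs in all participants in this clinical trial will be recorded at every visit". All serious adverse events are reported onward, and death is listed among them.
- Safety outcomes: "Routine physical examination will be performed on all participants during the study period". The laboratory tests "will be performed as subclinical measures to assess safety for all participants".

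The Study objective section puts safety in the primary objective beside cardioprotection. The second hypothesis is that the herb "will be safe at the dosage used in this trial".

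**The concern.** The article collects safety data on all participants but, where it describes analysis, offers only a set conditioned on completing the trial. Patients who leave early are plausibly informative about harm. Someone unwilling to continue the granules may have tolerated them badly, and in a cardiotoxicity trial starting a heart medicine may itself mark an adverse event. A patient who dies before the end cannot complete, so a completers-only set contains no such deaths by construction.

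If that set were used for adverse events, the comparison behind the safety half of the primary objective would depend on who stayed, which can itself be affected by treatment. Randomisation would no longer protect it. Leaving the population open until the data are seen would also allow it to be chosen in the light of the results.

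**Working it through.** **1. How many patients are at issue.** Inputs from the sample size section: 120 randomised, 60 per arm, 20% dropout.
- The plan's own dropout step is consistent with 48 completers per arm: 48 / (1 − 0.20) = 60 per arm, or 96 / (1 − 0.20) = 120 in total.
- Expected outside a completers set: 120 × 0.20 = 24 patients, or 12 per arm if losses are equal.

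**2. What each part of the article settles.**

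| Section | What it governs | Whom it covers |
|---|---|---|
| Safety outcomes | Examination and laboratory tests | All participants |
| Data and safety monitoring | Recording adverse events; reporting serious ones | All participants; all serious events |
| Statistical analysis, sentence 1 | Who performs the analysis, adverse events included | No population stated |
| Statistical analysis, sentence 2 | Analysis labelled intention-to-treat | Completers |

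The first two rows concern collection and reporting and give no denominator for comparing the arms. Only the last row names an analysis population.

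**3. What conditioning on completion can do.** The article gives no adverse-event rates and no reasons for stopping, so every count here is an assumption. Take 60 dosed per arm, with a toxicity in 18/60 (30%) on the herb and 12/60 (20%) on placebo. The true excess is 18/60 − 12/60 = 10.0 points. Suppose that only patients with the toxicity stop, S_h on the herb and S_p on placebo. The excess among completers is then

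(18 − S_h)/(60 − S_h) − (12 − S_p)/(60 − S_p).

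| Stops, herb v placebo | Completers, herb | Completers, placebo | Excess |
|---|---|---|---|
| 9 v 3 | 9/51 = 17.6% | 9/57 = 15.8% | 1.9 points |
| 8 v 4 | 10/52 = 19.2% | 8/56 = 14.3% | 4.9 points |
| 6 v 4 (one third of cases in each arm) | 12/54 = 22.2% | 8/56 = 14.3% | 7.9 points |
| 6 v 6 | 12/54 = 22.2% | 6/54 = 11.1% | 11.1 points |

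The same 10.0-point excess can almost vanish or grow slightly, depending on the stopping pattern.

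**4. A second assumed case, at the planned dropout.** Let 12 patients per arm leave, with 3 adverse-event cases among the 48 completers in each arm. Add 6 withdrawals for adverse events on the herb and none on placebo. All randomised: (3 + 6)/60 = 15% against 3/60 = 5%. Completers: 3/48 = 6.3% in both arms. The difference disappears.

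**The case against.** The strongest reply is that the protocol never says adverse events are analysed in completers. The first sentence of the Statistical analysis section says only who does the work, and the completers sentence is attached to the intention-to-treat label. The link between them rests on their being adjacent and on no other set being named. The safety sections say all participants throughout, and a condensed article may leave the definition of a safety set to the full protocol or the analysis plan.

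Most of this stands. A reader might infer that the plan excludes patients who stop because of harm from the safety comparison; the document does not say so. The lack of a separately named safety set would not be a finding by itself. The withdrawal rule mentions neither intolerance nor any end to adverse-event follow-up, so harm as a reason for stopping is plausible but not stated.

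Two further inferences also go beyond the text. The document does not apply last observation carried forward to adverse-event counts. Nor must a completers analysis flatter the herb: the 6 v 6 case above moves the excess the other way.

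What the reply does not remove is that the article does fix a population, fixes it badly, and places it directly after the sentence covering adverse events. Collecting data on everyone does not settle who enters the comparison. Correcting the efficacy population alone would remove the misleading sentence but still leave the adverse-event population unstated.

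**Conclusion.** The point holds as an ambiguity with a real consequence. It does not show that adverse events are expressly restricted to completers. Under the only analysis set named, patients who die, stop or are withdrawn would be left out of the adverse-event comparison: about 24 of 120 at the anticipated dropout, assuming that dropout means not completing. This sits badly with safety sections that cover all participants and with safety being part of the primary objective.

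The bias could be large if harm-related stopping differs by arm. Its size and direction cannot be computed from the document, and the figures from 1.9 to 11.1 points illustrate assumed counts only. Calling a completers analysis intention-to-treat is an error in its own right, and it is the source of the ambiguity.

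**What to change.** In the Statistical analysis section, correct the completers sentence so that the intention-to-treat analysis means all randomised patients in their allocated arms. Then add a sentence such as: Adverse events and laboratory safety data will be analysed in every randomised patient who took at least one dose of granules, using all data recorded up to week 20 or last contact, whether or not the patient completed the trial or was withdrawn.

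Week 20 is the last assessment listed in the abstract. The added sentence brings the analysis into line with Safety outcomes and with Data and safety monitoring.

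The cost is two sentences of text. No new data are needed, because the safety sections already provide for collection in all participants. The safety profile may look slightly less favourable. The article reports recruitment as ongoing, so the change should be made before unblinding.

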### Randomization, allocation concealment, and blinding

To minimize selection bias, all eligible patients will be randomized in a 1:1 ratio to the treatment group or control group. We will use IBM SPSS software version 19 (IBM, Armonk, NY, USA) for group allocation according to a randomization list. Randomization will be performed by a professional, independent statistician who is not involved in the recruitment process of the study. The randomization codes will be concealed in sequentially prepared, coded, individual, opaque envelopes prepared by research assistants who are not involved in the recruitment process. The envelopes will be kept secure in the Good Clinical Practice (GCP) Centre of Longhua Hospital and will not be opened until after statistical analysis or in the case of a medical emergency. The study participants, study investigators, other research team members, pharmacists, nurses, and technicians will remain blinded to the allocation of study medication versus placebo.

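### The analysis labelled intention-to-treat is limited to trial completers, and the protocol's own withdrawal rules tie completion to the cardiac outcome

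*Protocol article*

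**What the plan says.** The Statistical analysis section fixes the population: "Intention-to-treat (ITT) analysis will be carried out in all participants who complete the clinical trial". The sentence after it fixes the handling of missing values: "Missing data will be adjusted for using the last observation carried forward (LOCF) principle to obtain a complete database". Neither refers to the other, and the article does not define what completing the trial means.

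Three other sections bear on who would be left out:

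- Randomization, allocation concealment, and blinding: "all eligible patients will be randomized in a 1:1 ratio to the treatment group or control group".
- Sample size calculation: "Anticipating a 20% dropout rate, a total of 120 patients, with 60 patients in each group, will be recruited for the pilot study".
- Intervention: "Participants will be withdrawn if they take any other CHM or Western medication to treat heart disease during the 12-week intervention period". Refusal of the granules is a second ground for withdrawal in the same section.

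The primary outcome (Outcomes section) is heart failure, either clinical (assessed by NYHA class) or subclinical (defined by ejection fraction). Study drug is given for 12 weeks, and the Abstract schedules assessments up to week 20.

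**The concern.** Intention-to-treat means that everyone randomised is analysed in the allocated arm. A set conditioned on completion is a different set, so the label and the definition contradict each other within one sentence. This is a stated rule, not a detail left to an analysis plan.

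Randomisation makes the arms comparable at allocation. Whether a patient completes is settled later and can depend on treatment, on tolerability and on cardiac events. Here the link to the outcome is explicit. A patient who develops heart failure and is given medication for it meets a withdrawal criterion. If withdrawal counts as non-completion, that patient's event may never be analysed. Unwillingness to take the granules is the second route out, and it can differ between arms. At stake is the primary comparison, reported under a name that tells readers it is protected against this problem.

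**Working it through.** **Inputs from the article.** 120 patients randomised 1:1, 60 per arm; anticipated dropout 20%; two-tailed significance level 0.05. The article gives no event rate, no dropout by arm and no definition of completion.

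**Step 1: the plan's own figure.** No sample size before dropout is stated. Working back, 60 × (1 − 0.20) = 48 per arm, and 48 / 0.80 = 60. This agrees with the stated 120 but is circular, so it confirms nothing about the design. It does give the number of completers that the plan implies.

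**Step 2: how many patients fall outside the set.** Assume that dropout means non-completion and occurs at the planned rate.

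- Left out: 120 × 0.20 = 24, or 12 per arm if balanced.
- Analysed: 120 − 24 = 96, or 48 per arm if balanced.

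**Step 3: does the missing-data sentence repair this?** There are two readings.

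- The set is completers. Carrying the last observation forward then fills gaps only within those 96, and the 24 stay out.
- Dropouts were meant to be carried forward. All 120 are then analysed, and the completer sentence is wrong.

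The text therefore allows 96 or 120 patients under the same label, and the choice could be made after data are seen.

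**Step 4: what the exclusion can do.** The counts here are assumptions, chosen so that there is no true effect. Each arm has 60 patients, 12 events (20%) and 12 dropouts. Let *a* and *c* be the events among active and control dropouts. The completer rates are (12 − a)/48 and (12 − c)/48. RR is active over control; the true RR is 1.0.

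| a (active) | c (control) | Active completers | Control completers | RR | Chi-square p |
|---|---|---|---|---|---|
| 0 | 0 | 12/48 (25.0%) | 12/48 (25.0%) | 1.0 | – |
| 2 | 8 | 10/48 (20.8%) | 4/48 (8.3%) | 2.5 | 0.08 |
| 8 | 2 | 4/48 (8.3%) | 10/48 (20.8%) | 0.40 | 0.08 |
| 6 | 0 | 6/48 (12.5%) | 12/48 (25.0%) | 0.50 | 0.12 |
| 0 | 6 | 12/48 (25.0%) | 6/48 (12.5%) | 2.0 | 0.12 |
| 9 | 0 | 3/48 (6.3%) | 12/48 (25.0%) | 0.25 | 0.011 |

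For the second row, without continuity correction: χ² = 96 × (4 × 38 − 10 × 44)² / (48 × 48 × 14 × 82) = 96 × 82,944 / 2,644,992 = 3.01, so p is about 0.08.

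**Step 5: other event rates.** At an assumed 10% (6/60 per arm), losing 3 events from the active arm only gives 3/48 versus 6/48. At 30% (18/60 per arm), losing 9 gives 9/48 versus 18/48. Both have RR 0.5, and RR 2.0 if the loss is in the control arm instead.

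**The case against.** The strongest defence is that the completer sentence is loose drafting. The next sentence aims at a complete database, which suggests that dropouts were to be carried forward. The planned Kaplan-Meier and Cox analyses can also use incomplete follow-up by censoring. This stands as a plausible account of intent, but not as a repair. No sentence returns withdrawn patients to the set, and survival methods can use only the patients who are in it.

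The illustration is also open to challenge. Its counts are invented, and the 8-versus-2 split, already a strong imbalance, does not reach the 0.05 level. That is fair: it shows that bias is possible, not how large it is likely to be. Row one of the table shows that equal losses leave the ratio at 1.0 when there is no true effect.

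Finally, the article calls the trial a pilot for a larger study. That tempers the consequences. It does not remove them, because the stated primary objective is cardioprotection and safety.

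Three stronger readings are tempting and unsupported:

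- **Nonadherent patients are also removed.** A reader might infer this from the compliance item among the exclusion criteria together with "Participants who return more than 10% of the total allotted granules will be defined as nonadherent". That item stands among the eligibility criteria and reads naturally as a judgement at screening. The granule-return rule only classifies patients and has their reasons recorded. No section takes them out of follow-up or analysis.
- **Exactly 24 patients will be lost.** The 20% is an anticipated dropout rate. Completion could mean finishing 12 weeks of granules or attending the week-20 visit.
- **The bias favours the herb.** Nothing in the article fixes its direction.

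**Conclusion.** The point holds. The population sentence describes a completers analysis and calls it ITT, and the missing-data sentence either leaves that unchanged or contradicts it. Because one withdrawal criterion is treatment for heart disease and the primary outcome is heart failure, the exclusion can remove the events that the trial is meant to count.

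The extent is 24 of 120 patients, on the assumption that dropout equals non-completion at the planned 20%. The link to the outcome assumes that withdrawn patients count as non-completers, which the article does not say outright. The likely size and direction of bias cannot be derived from it. The matter should be corrected before analysis, since it governs the main comparison and the change to the text is small.

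**What to change.** 1. Define the primary analysis set as all randomised patients, analysed in the allocated arm regardless of adherence, withdrawal or completion. Reword the missing-data sentence so that it says explicitly how it applies to patients who leave early.
2. Count every primary-outcome event observed up to withdrawal, and keep non-completers' data in the planned Kaplan-Meier and Cox analyses. Censoring at withdrawal is not a full answer by itself, since withdrawal may be related to the outcome.
3. Record outcomes at the scheduled visits after withdrawal where the patient agrees. This concerns data collection only; the withdrawal criteria themselves need not change for it.
4. Report completers, or adherent patients, only as a labelled sensitivity analysis.

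The cost is a few sentences in the analysis and follow-up text and no additional patients. It is not free of data work: some withdrawn patients must be followed, and some missing outcomes will remain and need a stated method.

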## Abstract

**Background:**

Anthracyclines, alone or in combination with other drugs, are among the most effective chemotherapeutic agents to treat breast cancer both in the adjuvant and neoadjuvant setting. Unfortunately, anthracycline-associated dose-dependent cardiotoxicity is a limiting factor in clinical use. Extensive efforts have been devoted to identifying strategies to prevent anthracycline-induced cardiotoxicity. However, most cardioprotective agents have shown little effect in clinical trials. Herbal medicines are pure, natural substances that have been used for centuries in many countries, including China. This trial aims to evaluate the cardioprotective effects and safety of *Platycodon grandiflorum* granules compared to placebo granules in patients with early breast cancer receiving anthracycline-based chemotherapy.

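### LOCF is the only missing-data method named and sits beside a completers-only rule, so dropouts without an event are either carried forward as event-free or deleted, and either can bias the primary comparison

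*Protocol article*

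**What the plan says.** Two adjacent sentences in the protocol article, Statistical analysis, decide what happens to patients with incomplete data:

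- Analysis set: "Intention-to-treat (ITT) analysis will be carried out in all participants who complete the clinical trial".
- Missing data: "Missing data will be adjusted for using the last observation carried forward (LOCF) principle to obtain a complete database".

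No second missing-data method and no sensitivity analysis is named. The same section plans Kaplan-Meier curves and a log-rank test on the cumulative anthracycline dose at which cardiotoxicity occurs, and a Cox model. It does not say how LOCF and censoring are to work together.

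Other sections bear on this:

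- Sample size calculation: "Anticipating a 20% dropout rate, a total of 120 patients, with 60 patients in each group, will be recruited for the pilot study".
- Abstract, Background: "anthracycline-associated dose-dependent cardiotoxicity is a limiting factor in clinical use". The main Background section also places the risk chiefly at high cumulative doses.
- Hypothesis: the expected benefit is fewer patients with cardiac damage at 12 weeks. The Abstract lists visits at baseline and weeks 3, 6, 9, 12, 16 and 20.
- Intervention: a participant who takes another herbal or Western treatment for heart disease during the 12 weeks is withdrawn. The text does not say whether this ends study medication only or also follow-up.

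**The concern.** LOCF assumes that a patient's state stays where it was last seen. The protocol describes the opposite course, with damage that depends on dose. A patient who leaves at week 3 or 6 with an acceptable ejection fraction would be carried to week 12 or 20 as free of heart failure, on the strength of a scan taken before most of the exposure.

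The completers sentence leads elsewhere. If it governs, dropouts leave the analysis altogether and LOCF can fill only visits missed by patients who finish. The statistician could follow either sentence, and the results would differ.

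Neither route is safe if the reasons for leaving are linked to the heart. The withdrawal rule in the Intervention section makes such a link plausible: a patient treated for an emerging cardiac problem before the endpoint is recorded may become one of the missing. At stake is the estimated risk of the primary outcome in each arm and, if dropout differs in amount or kind between arms, the comparison itself.

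**Working it through.** **The protocol's own figures.** Dropout of 20% in 60 per arm is 0.20 × 60 = 12 patients, or 24 of 120. The inflation step is consistent: 60 × 0.80 = 48 and 48 / 0.80 = 60. The 48 is back-calculated, so this does not check the sample size. The article gives no event rate, effect size or power from which 120 could be reproduced.

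**Illustration on a proportion.** Only the 20% dropout comes from the protocol; all other inputs are assumed.

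- p = 0.20: true risk over full follow-up
- d = 0.20: dropout
- r: dropouts' risk relative to completers' risk
- f: share of dropouts' events seen before they leave (these events are kept)

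Completers' risk: p0 = p / [(1 − d) + d·r]. This is what the completers rule would report.

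LOCF-recorded risk: (1 − d)·p0 + d·f·r·p0.

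| r | f | Completers rule | LOCF | LOCF events missed per 60 |
|---|---|---|---|---|
| 1 | 0.5 | 20.0% | 0.8×0.20 + 0.2×0.5×0.20 = 18.0% | 1.2 |
| 1 | 0 | 20.0% | 0.8×0.20 = 16.0% | 2.4 |
| 2 | 0.5 | 0.20/1.2 = 16.7% | 0.8×0.1667 + 0.2×0.5×0.3333 = 16.7% | 2.0 |
| 2 | 0 | 16.7% | 0.8×0.1667 = 13.3% | 4.0 |
| 3 | 0 | 0.20/1.4 = 14.3% | 0.8×0.1429 = 11.4% | 5.1 |

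Across these rows LOCF misses from (0.20 − 0.18)/0.20 = 10% to (0.20 − 0.114)/0.20 = 43% of true events. The completers rule is unbiased only when dropouts have the same risk as completers (r = 1).

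**Effect on the comparison.** LOCF multiplies the true risk by [(1 − d) + d·f·r] / [(1 − d) + d·r]. If d, r and f are the same in both arms, the factor cancels and the risk ratio is unchanged. The same holds for the completers rule.

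Now let dropout differ, with no true effect (20% risk in both arms) and assumed dropout of 10% versus 30%:

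- LOCF, r = 1, f = 0: 0.9×0.20 = 18% versus 0.7×0.20 = 14%, a false difference of 4 points and a risk ratio of 0.14/0.18 = 0.78.
- LOCF, r = 1, f = 0.5: 19% versus 17%, risk ratio 0.89.
- LOCF, r = 3, f = 0: 15% versus 8.75%, risk ratio 0.58.
- Completers rule, r = 1: 20% versus 20%, no bias.
- Completers rule, r = 2: 0.20/1.1 = 18.2% versus 0.20/1.3 = 15.4%, risk ratio 0.85.

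Each false difference favours the arm with more dropout.

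**The case against.** Much of the case on the other side is sound.

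- **The two harms are alternatives.** If the completers rule governs, dropouts are gone and LOCF never reaches them. The LOCF figures above apply only if that sentence is set aside. This stands.
- **The sentences need not clash.** A reader might infer a flat contradiction. With six post-baseline visits a completer can miss one, and LOCF can fill that gap, so the two sentences can be read together. What remains is that the text does not say this, and that a completers-only set is mislabelled as intention-to-treat.
- **The named cardiotoxicity analysis is not a proportion.** A reader might infer that LOCF corrupts the Kaplan-Meier and Cox analyses. The article does not say that LOCF extends follow-up there. On a dose axis, carrying forward both the event-free status and the last recorded dose leaves the patient at that dose, which amounts to censoring. The interplay is unspecified rather than shown to be wrong. The 12-week hypothesis, however, is worded as a comparison of how many patients are affected, so a proportion is a natural reading.
- **The illustration rests on assumptions.** The article gives no event risk and a single overall dropout figure, with nothing on differential dropout.
- **Plain censoring is not a clean cure.** It may be informative, given withdrawal for heart-disease treatment. This stands and shapes the fix.
- **A SAP may set out further methods.** That would answer an omission. Here LOCF is stated as the rule.

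**Conclusion.** The concern holds in a limited form. The article fixes LOCF as its only missing-data method for a toxicity that it calls dose-dependent, beside a sentence that would exclude the patients who most need a rule. About 12 patients per arm are affected at the protocol's own dropout rate.

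Under the assumed 20% risk, LOCF would record 18% to 13.3% in the central cases and 11.4% in the most adverse one. This understates the risk within an arm. Distortion of the between-arm comparison is a further step, which needs dropout that differs between arms in amount or in its relation to outcome.

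Two stronger readings are not supported. One is that every dropout is recorded as free of toxicity: patients whose event was seen before leaving keep it. The other is that LOCF will make the herb look protective: nothing in the document says which arm would lose more patients or that the arms would differ.

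Should-fix rather than must-fix: the study is described as a pilot for a larger trial, and the direction and size of any bias between arms cannot be known from the document.

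**What to change.** 1. Define the primary analysis set as all randomised patients, and remove the restriction to completers.
2. Replace LOCF as the primary method. It may stay as a sensitivity analysis.
3. For heart failure, use every observed assessment, including those after withdrawal from study drug where available. In the Kaplan-Meier and Cox analyses, censor event-free patients at their last cardiac assessment, at the last observed cumulative dose. If a week-12 proportion is reported, use multiple imputation.
4. For continuous outcomes, use a mixed model for repeated measures on all observed visits.
5. Add one sensitivity analysis for informative censoring: a tipping point, or counting cardiac-related withdrawals as events. Counting every missing patient as an event would be too blunt: it could add up to 12 events per arm, as many as the 60 × 0.20 = 12 expected at the assumed risk.
6. Reconcile the withdrawal rule in the Intervention section with the analysis set, so that it is clear what data are kept for withdrawn patients. No clinical rule is proposed here.

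Cost: changed wording, some extra programming and slightly wider intervals, with no new data collection. Recruitment was still under way when the article was written, and allocation stays concealed until after the analysis except in a medical emergency, so the change can be made blind.
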